#### Secondary endpoints

Secondary endpoints include metastasis-free survival, generic and disease-specific patient-reported health-related QoL using validated questionnaires, oncologic safety, disease progression, disease-specific mortality, all-cause mortality, adverse events, operating time, hospital care stay, pathology results, resources use and productivity loss using validated questionnaires and cost-effectiveness. The questionnaires will be completed online using a secure web-based module at baseline and at specific follow-up intervals, that is, 6 weeks, 3 months, 6 months, 12 months and annually thereafter for up to 60 months.

For the patient-reported health-related QoL outcomes, patients will use a set of six validated questionnaires. QoL is measured at baseline and at set points during follow-up.

For the other secondary endpoints the following questionnaires will be used: European Organisation for Research and Treatment of Cancer QoL questionnaire prostate 25 (EORTC QLQ PR-25), international consultation on incontinence questionnaire (ICIQ), international prostate symptom score (IPSS), sexual health inventory measurement international index of erectile dysfunction (SHIM IIEFF-5), EuroQoL 5 dimensions five-level version (EQ-5D-5L). The EORTC QLQ PR-25 is a questionnaire to assess sexual problems and functioning, micturition, bowel symptoms and hormonal treatment side effects. This questionnaire contains 25 questions regarding those aspects. The ICIQ is used to assess urinary function and its impact on QoL and contains four questions. IPSS is a questionnaire for assessment of the degree of lower urinary tract symptoms and QoL. This score consists of seven questions and an overall score on quality of miction. The SHIM IIEF-5 used is the 5-item version of the IIEF. This questionnaire assesses erectile function and contains five questions. The EQ-5D-5L is a questionnaire that assesses general health in five dimensions. These dimensions are mobility, self-care, usual activities, pain/discomfort and anxiety/depression. Further, a visual analogue scale (VAS) is used to provide a quantitative measure of the perception of overall health of a participant.

Two questionnaires will additionally be used regarding cost-effectiveness analyses. The iMTA productivity cost questionnaire (iPCQ) is used to assess productivity loss in terms of absence from work due to illness. The iMTA medical costs questionnaire (iMCQ) is used to determine healthcare consumption, including hospital visits and domestic help.

In the secondary endpoints, clinical outcomes are included, such as operating time and hospital care stay. Operating time will be registered for focal therapies as the time between the start of imaging and the last performed imaging and for RP as the time from the start of incision until closing. For RT, we will register the type of radiation given. Further, data will be collected on treatment-related complications occurring during or after the procedure. During follow-up oncologic safety, in terms of disease progression, metastasis-free survival, disease-specific mortality and all-cause mortality, will be assessed using PSA, MRI and biopsies, as well as data from a national registry. Pathology results from surgery and biopsies will be collected. In addition to the questionnaires for cost-effectiveness analysis, hospital resource use will be recorded.

### Patient characteristics

Patients aged 40 years and older with localised unilateral dominant PCa, a PSA≤20 ng/mL and normally eligible for general anaesthesia will be included in this study. All inclusion and exclusion criteria are listed in table 1. Patients will be included after being diagnosed with intermediate-risk PCa and having completed the diagnostic work-up according to national guidelines. At a minimum, all patients will have undergone clinical examination, PSA testing, prostate MRI and prostate biopsies. Additional staging procedures are not part of standard staging for this risk category in the Netherlands.

**Table 1 T1:** Inclusion and exclusion criteria. To be able to participate in this study, patients must meet all inclusion criteria and cannot meet any of the exclusion criteria

Inclusion criteria	Exclusion criteria
Men, age of 40 years or over, with unilateral clinically significant intermediate-risk PCa or dominant unilateral clinically significant intermediate-risk and small contralateral low-risk (ISUP) one disease	Unfit for general anaesthesia or radical surgery
Gleason score of 7 (3+4 or 4+3; ISUP grade 2/3)	Low-volume low-risk disease (≤4 mm Gleason score of≤6/ISUP grade 1)
PSA level of≤20 ng/mL	High-risk disease (Gleason score of≥8/ISUP grade>3)
Clinical stage≤T2b disease	Clinical cT2c or T3 disease (extracapsular PCa)
Life expectancy of≥10 years	Men who have received previous active therapy for PCa
Men with a prostate size≤5 cm in sagittal length or≤6 cm in axial length	Men with evidence of extraprostatic disease
Fit, eligible and normally destined for radical surgery or radiotherapy	Men with an inability to tolerate transrectal ultrasound
No concomitant cancer	Cardiac pacemaker
No previous treatment of their prostate	Metal implants/stent in the urethra or prostate
An understanding of the Dutch language sufficient to receive written and verbal information about the trial, its consent and the study questionnaires	ASA≥4
	Prostatic calcifications/cysts that interfere with effective delivery of TULSA/HIFU based on MR
	Men with renal impairment and a glomerular filtration rate (GFR) of<30 mL/minute/1.73m2
	Unable to give consent to participate in the trial, as judged by the attending clinicians

GFR, glomerular filtration rate; HIFU, high-intensity focused ultrasound; PCa, prostate cancer; PSA, prostate-specific antigen; TULSA, transurethral ultrasound ablation.

### Randomisation

Eligible participants who provide informed consent will be randomised in a 1:1 ratio to focal therapy or radical whole-gland treatment using a computer-generated allocation sequence. Randomisation will be stratified by centre, Gleason score (3+4 or 4+3) and age group to ensure balanced distribution of participants across treatment arms within each stratum.

Random block sizes will be used within each stratum to maintain allocation concealment. The allocation sequence will be implemented via a centralised web-based system to maintain blinding of investigators and study personnel involved in enrolment.

### Interventions

The therapies within the intervention group are HIFU, TULSA and IRE. If a patient is assigned to focal therapy, the treatment a patient receives is based on the centre where the inclusion took place. This means that a patient is not able to choose what kind of focal therapy will be received in case of randomisation for focal therapy. The control group consists of RP or RT. If a patient is allocated to radical treatment, the patient will receive treatment as per current clinical practice in the Netherlands according to the Dutch guidelines. For RP, different types of approaches are possible, including nerve-sparing and non-nerve-sparing options, depending on tumour characteristics and anatomical considerations. Patients receiving RT will be treated as per national guidelines. Therapies administered can include RT with hypofractionation (28 fractions with 2.5 Gy, total dose of 70 Gy or 20 fractions with 3.1 Gy, total dose of 62 Gy) and RT with ultrahypofractionation (5 fractions with 7.25 Gy, total dose of 36.25 Gy). All RT regimens provide bio-equivalent doses similar to conventional RT consisting of 35 fractions with 2 Gy. According to the current national guidelines, the addition of androgen deprivation therapy (ADT) is not recommended for patients with intermediate-risk PCa with a PSA level of 20 ng/mL or lower. Patients eligible for both RP and RT are provided with evidence-based information, including a decision aid, to support shared decision making. The final treatment choice is made jointly by the patient and the urologist.

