We expect several challenges in executing our study. First, in previous studies no differences have been observed between the different focal therapies,^8 14^ but these techniques have not been directly compared within a single study. We aim to gain more insights into potential existing differences between the different modalities. For this aim, we will perform exploratory analyses for the focal therapies versus the radical treatments. Adjustment for centre will not be possible in these analyses since the type of focal therapy is centre-dependent; also the offered standard of care modalities differ between the centres. Furthermore, the different centres may have different perioperative protocols or complications.

Second, another complexity in this study is the difference in follow-up protocols between the treatment arms. In the standard of care arm, PSA is used as the primary follow-up marker. After RP the PSA level is expected to become undetectable within 2 months.^20^ PSA levels in RT drop more slowly compared with RP. No optimal cut-off value has been determined, but in current clinical practice a PSA<0.5 ng/mL is set as a favourable outcome after RT.^21^ However, after focal therapy, PSA monitoring becomes less reliable since the untreated part of the prostate continues to function and produce PSA as before. This necessitates a different follow-up approach for patients in the focal therapy arm. In this trial, we will perform MRI and biopsies as an additional part of the follow-up after focal therapy, as MRI has proven effective in detecting new or recurrent lesions in the prostate. Recently, scoring systems have been developed to evaluate post-focal treatment MRIs, in which the likelihood of recurrent disease is scored.^22 23^ These systems offer guidance on subsequent steps, ranging from continued observation to additional diagnostic procedures such as biopsies. We will implement such a scoring system (PI-FAB scoring system) alongside standardised biopsies at 1-year follow-up to confirm the presence or absence of a tumour after focal treatment. This approach allows us to validate the scoring system by comparing its outcomes with biopsy results.

Third, QoL will be assessed using patient-reported questionnaires, which may be subject to bias such as recall bias and response bias. These questionnaires are, however, validated, and the use of these questionnaires aims to reduce these biases.

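### Centre can be adjusted for when each focal therapy is compared with radical treatment; any focal-versus-RP or focal-versus-RT contrast would need the intended modality recorded before allocation

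*Protocol article*

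**What the plan says.** **Allocation.** Under Randomisation, men are "randomised in a 1:1 ratio to focal therapy or radical whole-gland treatment". The same section adds: "Randomisation will be stratified by centre, Gleason score (3+4 or 4+3) and age group". The radical treatment a man would otherwise have is not a stratification factor.

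**Centres.** Design states that every centre offers a single focal technique as well as radical treatment, with radiotherapy by referral. Recruitment gives two centres each to TULSA, IRE and HIFU.

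**Choice of radical treatment.** Interventions begins the control-arm description with "If a patient is allocated to radical treatment, the patient will receive treatment as per current clinical practice in the Netherlands" and ends it with "The final treatment choice is made jointly by the patient and the urologist". Table 1 requires only that men be "Fit, eligible and normally destined for radical surgery or radiotherapy", without asking which.

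**Exploratory analyses.** The Discussion wants insight into differences between modalities, and for that "we will perform exploratory analyses for the focal therapies versus the radical treatments". It continues: "Adjustment for centre will not be possible in these analyses since the type of focal therapy is centre-dependent", and gives a second reason: "also the offered standard of care modalities differ between the centres". It does not mention selection by the choice of patient and urologist.

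**The concern.** There are two separate problems, both confined to the exploratory analyses.

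First, the article says centre adjustment is impossible in a contrast where the design provides for it. If one focal therapy is then compared with radical patients from all six centres, differences between centres enter the estimate. The Discussion itself expects such differences, in perioperative protocols, complications and the radical modalities on offer.

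Second, if RP or RT is chosen once a man knows he is in the radical arm, the focal arm contains no identifiable men who would have chosen RP, and none who would have chosen RT. Comparing all focal men with those who received RP, or with those who received RT, sets an unselected group against a self-selected one. The result mixes the treatment effect with whatever distinguishes men who choose surgery from men who choose radiotherapy.

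**Working it through.** **1. Is centre adjustment possible?** It depends on the contrast.

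- *One focal therapy against radical treatment.* Each centre randomises to both arms, so a within-centre difference can be estimated in both centres giving that therapy and then combined. Adjustment is possible.
- *One focal therapy against another.* No centre gives two focal therapies, so centre and modality cannot be separated. Adjustment is not possible.

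The sentence is attached to the first contrast but is true only of the second.

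**2. What is at stake in the choice of controls?** Assume equal recruitment across the six centres. If controls come from all six, 4/6 = two-thirds come from centres that do not give the focal therapy in question. The bias is then two-thirds of any outcome gap between those centres and the therapy's own. Own-centre controls remove it at some loss of precision. With 178/3 ≈ 59.3 men per arm per therapy and SD 20 (Sample size):

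- own-centre controls: 20 × √(2/59.3) ≈ 3.7 points
- controls from all centres: 20 × √(1/59.3 + 1/178) ≈ 3.0 points

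**3. How large could choice bias be?** Let *s* be the share choosing RP and *g* the outcome gap between RP-choosers and RT-choosers under the same treatment. Comparing all focal men with RP recipients is biased by (1 − *s*) × *g* in size. The RT contrast is biased by *s* × *g* in the opposite direction. The article gives neither *s* nor *g*; all values here are assumptions.

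- FACT-P, *s* = 0.5, *g* = 2 to 10 points: bias 1 to 5 points, against an MCID of 8.
- Failure, RP contrast, *s* = 0.3 to 0.7, *g* = 5 to 10 percentage points: bias from 0.3 × 5 = 1.5 to 0.7 × 10 = 7 points, against a 15-point margin.

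A simulation of 4,000 trials used *s* = 0.5, radical-arm failure of 10% in RP-choosers and 20% in RT-choosers, and a true difference of 5 points. All focal men against RP recipients averaged 10.1 points. Focal against radical among men intending RP averaged 5.0.

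**4. What precision would remain within intended modality?** The trial's own size is reproduced first. No event rates are stated, but assumed failure of 15% (radical) and 20% (focal) gives, per arm,

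(1.645 + 0.842)² × (0.15 × 0.85 + 0.20 × 0.80) / (0.15 − 0.05)² ≈ 178,

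that is 356 in total, as stated. With an even RP/RT split:

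| Men with intent recorded | Per arm per stratum | FACT-P SE | QoL power, one-sided 5%, difference 8 | Non-inferiority power |
|---|---|---|---|---|
| All 356 | 89 | 20 × √(2/89) = 3.0 | 85% | 55% |
| 356 − 110 = 246 | 61.5 | 20 × √(2/61.5) = 3.6 | 72% | 43% |

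The second row uses the same normal approximations: QoL Φ(8/3.607 − 1.645) = Φ(0.57); non-inferiority Φ(0.10/√(0.2875/61.5) − 1.645) = Φ(−0.18). The unmatched contrast, 178 against 89, has SE 20 × √(1/178 + 1/89) = 2.6, but carries the bias in step 3. With all 356 men and strata of 30% and 70%, non-inferiority power is 39% and 67%.

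**The case against.** The strongest reply is that the article does not clearly plan focal-versus-RP or focal-versus-RT contrasts. The stated interest is in differences between the focal modalities, the design is presented as a comparison of groups of therapies, and no such contrast is listed among the secondary endpoints. Each focal therapy against the pooled radical arm of its own centres is not confounded by the RP/RT choice. This stands, so the choice point has to be conditional. The plural in "we will perform exploratory analyses for the focal therapies versus the radical treatments" leaves the other reading open without establishing it.

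It is also fair that the timing of the choice is inferred from how Interventions is laid out. Men must already be destined for surgery or radiotherapy, and the full protocol may record which. A condensed article's silence about a baseline field is not an error.

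On centre, the sentence is a valid limitation for focal-versus-focal comparisons and should be kept for those. With 1:1 allocation within centre, leaving out adjustment when the controls are a therapy's own centres would cause little confounding. The main gain comes from using those controls, and stratification then respects the design. None of this rescues the claim that adjustment is impossible against radical treatment.

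The size of the choice bias is assumed throughout. Since QoL is collected at baseline, ordinary baseline adjustment would remove much of a baseline FACT-P imbalance; the unmeasured remainder is not quantified.

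**Conclusion.** The point holds in two parts of different strength. The statement on centre is wrong for the contrasts it is attached to, and this follows from the article's own Design, Randomisation and Recruitment sections without any assumption. The choice point is conditional: if focal-versus-RP or focal-versus-RT contrasts by treatment received are made, they are non-randomised. Their bias would be 1 to 5 FACT-P points under an assumed even split and an assumed gap of 2 to 10 points.

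A reader might infer that the main result is compromised. It is not: both co-primary analyses compare whole randomised arms by intention to treat, and the RP/RT choice does not bias them. Nor do the documents show that modality-specific contrasts are firmly planned, or that intent goes unrecorded. This is an improvement to exploratory analyses only.

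**What to change.** 1. Compare each focal therapy with the radical arm of its own two centres, by randomised arm and stratified by centre. Limit the sentence on centre adjustment to focal-versus-focal comparisons. This needs wording only; the price is the wider standard error in step 2 (about 3.7 instead of 3.0 points with equal recruitment).

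2. If focal-versus-RP or focal-versus-RT contrasts are intended, and unless the full protocol already does this, add one baseline field. For each remaining man, before allocation is revealed, record which radical treatment he and his urologist would choose. Analyse focal against radical by randomised arm within intended modality, whatever treatment was received. If they are not intended, say so.

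The second change has costs and limits. The decision-aid discussion moves ahead of randomisation. The roughly 110 men enrolled by October 2025 may lack the field, and the number grows with delay. With about 246 men left and an even split, the FACT-P standard error per stratum is about 3.6 points instead of 3.0. Non-inferiority within strata stays underpowered. RP and RT keep different failure definitions, so the two oncological contrasts could not be set directly against each other, and neither RP versus RT nor one focal therapy versus another becomes a randomised comparison.

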### Recruitment

Patients will be recruited from the six participating centres and their regional networks. Two of the including centres will perform TULSA, two will perform IRE and two centres will perform HIFU. One of the centres that performs HIFU collaborates with the including hospital in which the usual care arm will be performed.

#### Consent

All potential participants receive verbal and written information. After 7 days a member of the research team has telephone contact with the potential participant. If the patient is still interested in participating in the study, the informed consent papers (onlinesupplemental material 1  2 - (‘Subject Information Participation_ENFORCE’ and ‘Informed consent form_ENFORCE’) are signed in duplicate by the patient. After receipt of the signed papers, these are also signed by a research team member, which makes the enrolment in the study official.

### Analysis

Descriptive statistics will be used to summarise the data. For the oncological effectiveness, a one-sided 95% upper confidence bound will be created for the percentage difference in pathologically proven recurrent disease and/or (indication for) re-treatment (salvage treatment). If this bound is less than the non-inferiority margin of 15%, focal therapy will be declared to be non-inferior to usual care, that is, RP/RT. For the QoL, outcome differences between the two groups will be calculated with 95% CIs. All data will be analysed according to the intention-to-treat principle, including all randomised participants in the groups to which they were originally assigned, regardless of protocol deviations or loss to follow-up. In addition, to test robustness of the results, per-protocol and as-treated analysis will be performed regarding oncological effectiveness and QoL.

Furthermore, for secondary QoL outcomes, individual item responses will be used to derive the proportion of men reporting a moderate or big problem (or equivalent).

Metastasis-free survival, disease progression, disease-specific mortality and all-cause mortality will be presented with Kaplan-Meier curves. Procedure time and hospital care stay will be summarised using descriptive statistics. Treatment-related complications will be recorded according to the Clavien-Dindo classification. An overall risk difference for the overall complication rate and a 95% CI, and a risk difference per complication and their corresponding 95% CIs will be calculated. Pathology results will be summarised using descriptive statistics.

Cost-effectiveness will be performed from a societal perspective as per Dutch guidelines for economic evaluation.^18^ Costs will be calculated according to the Dutch guideline for costing research. Average costs will be calculated in both groups and differences will be calculated inclusive of 95% CIs. Effectiveness will be measured in terms of quality-adjusted life years (QALYs). These will be based on the utility scores as measured with the EQ-5D-5L, using the area under the curve method. Incremental cost-effectiveness ratios will be calculated by dividing estimated differences in costs by differences in QALYs. Uncertainty will be addressed by means of non-parametric bootstrapping and, where relevant, one-way sensitivity analyses.

A detailed Statistical Analysis Plan will be developed and finalised prior to database lock, outlining all pre-specified analyses and methods for handling missing data.

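### Treatment-related complications would be reported only by allocated arm, so the plan gives no complication risks for the treatments men actually received

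*Protocol article*

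**What the plan says.** Three statements in the protocol article bear on this point.

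- **Population.** The Analysis section sets one rule: "All data will be analysed according to the intention-to-treat principle, including all randomised participants in the groups to which they were originally assigned". The rule holds whatever deviations or losses occur, and no exception is made for safety outcomes.
- **Supplementary populations.** As a robustness check, "per-protocol and as-treated analysis will be performed regarding oncological effectiveness and QoL". Complications are not on that list, and the article names no treated or safety population for them.
- **Complication endpoint.** Under Secondary endpoints, "data will be collected on treatment-related complications occurring during or after the procedure". The Analysis section adds: "Treatment-related complications will be recorded according to the Clavien-Dindo classification". The planned contrast is: "An overall risk difference for the overall complication rate and a 95% CI, and a risk difference per complication", each with a 95% CI.

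Further detail is deferred: "A detailed Statistical Analysis Plan will be developed and finalised prior to database lock".

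**The concern.** A complication of treatment can arise only in a man who was treated. If every randomised man is counted in his assigned group, a man who withdraws or declines before treatment enters the table as complication-free. A man allocated to radical treatment who has focal therapy instead brings a focal complication, or none, into the radical column, and the reverse holds for a switch the other way.

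The article plans a treatment-received analysis for its two co-primary outcomes, so it allows for departures from allocation. It leaves out the outcome most closely tied to the treatment actually given.

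The Discussion says the trial should inform whether focal therapy is reimbursed and taken into standard care. Readers will take the complication table as the risk of having each treatment, but under the stated rule it is the risk of being assigned to it. Both are legitimate quantities, and only the second would be reported.

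**Working it through.** The article gives no figure to reproduce here: it states no complication rate, no rate of not starting treatment and no crossover rate. Its one attrition figure, the 5% drop-out in the Sample size section, is a different quantity. All rates below are assumptions.

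**Formula.** Let pF and pR be the complication risks of focal and radical treatment among men who have them. Let uF and uR be the shares of each arm never treated, and cF and cR the shares of each arm that switch to the other treatment. Assume that switchers have the same risk as other men given that treatment. Then:

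- focal arm as allocated = (1 − uF − cF) × pF + cF × pR
- radical arm as allocated = (1 − uR − cR) × pR + cR × pF
- radical minus focal = (1 − cF − cR) × (pR − pF) − uR × pR + uF × pF

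The first term shows that crossover alone multiplies the difference by (1 − cF − cR), which pulls it towards zero at any plausible level. The other two terms show that non-treatment in the riskier arm narrows the difference and non-treatment in the safer arm widens it.

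**A. Radical non-starters only.** pR = 30%, pF = 15%, difference by treatment received 15.0 points, focal arm fully adherent.

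| Radical arm not starting radical | Half untreated, half focal | Difference | All untreated | Difference |
|---|---|---|---|---|
| 0% | 30.0% | 15.0 | 30.0% | 15.0 |
| 5% | 0.95 × 30 + 0.025 × 15 = 28.9% | 13.9 | 0.95 × 30 = 28.5% | 13.5 |
| 10% | 0.90 × 30 + 0.05 × 15 = 27.75% | 12.75 | 0.90 × 30 = 27.0% | 12.0 |
| 20% | 0.80 × 30 + 0.10 × 15 = 25.5% | 10.5 | 0.80 × 30 = 24.0% | 9.0 |

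**B. Focal non-starters only.** Same risks, 10% of the focal arm untreated: 0.90 × 15 = 13.5%. The difference is 30.0 − 13.5 = 16.5 points, wider than 15.0.

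**C. Crossover of 10% each way, nobody untreated.** pR = 25%, pF = 10%. Focal arm: 0.90 × 10 + 0.10 × 25 = 11.5%. Radical arm: 0.90 × 25 + 0.10 × 10 = 23.5%. The difference falls from 15.0 to 12.0 points, while the focal arm's rate rises from 10.0% to 11.5%.

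**D. Focal treatment riskier.** pF = 25%, pR = 15%, 5% untreated in each arm, 5% switching from focal to radical and 15% from radical to focal. Focal arm: 0.90 × 25 + 0.05 × 15 = 23.25%. Radical arm: 0.80 × 15 + 0.15 × 25 = 15.75%. The focal excess falls from 10.0 to 7.5 points.

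**Scale against sampling error.** With 356/2 = 178 men per arm and risks of 30% and 15%, the 95% CI half-width is 1.96 × √[(0.30 × 0.70 + 0.15 × 0.85)/178] ≈ 8.5 points. The shift at 5% non-starters (half untreated, half focal) is about 1.1 points.

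**The case against.** The strongest reply is that an article condenses a plan. The intention-to-treat sentence stands in the paragraph on the co-primary outcomes, the abstract ties intention-to-treat to the primary analyses, and a treated population for safety is something a statistical analysis plan usually defines. If the article were silent, that would settle the matter. It is not silent: the sentence covers the data as a whole, and the next one lists the outcomes that also get an as-treated analysis. An analysis plan that added one for complications would be departing from the published rule.

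A second reply is that in a pragmatic trial the risk attached to the assigned strategy is a proper estimand and the only randomised comparison. That stands. It argues for keeping the intention-to-treat table and against demoting it, but not against a treatment-received table beside it.

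Third, the distortion may be small. That also stands: nothing in the article indicates how many men will not receive their assigned treatment.

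Two stronger readings are tempting and not supported. One is that intention-to-treat always understates procedural harm. Case B widens the contrast and case C raises the safer arm's rate, so only the lowering of an arm's own rate by its untreated men is general. The other is that a single overall rate hides serious events. The plan also gives a risk difference for each complication and records Clavien-Dindo grades, so the lack of a separate contrast by grade is not an error.

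**Conclusion.** The point holds as one about what will be reported. As written, the article gives treatment-related complications by allocation only, and so would not show the complication risks among men who had each treatment. Untreated men lower their arm's rate, crossover generally draws the arms together, and unequal non-treatment can move the difference in either direction.

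Under the assumed risks of 30% and 15%, with 5% to 20% of the radical arm not starting radical treatment (half untreated, half focal), the 15-point difference becomes about 13.9 to 10.5 points. At the low end this is small beside the sampling error; with full adherence it is nil. These figures rest on assumed rates and on switchers having the same risks as other men given that treatment. They do not show that focal harm in particular would be hidden: in the main illustration it is focal therapy's advantage that shrinks.

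**What to change.** Add complications to the outcomes that receive the as-treated analysis. Among men who started a treatment, grouped by the first treatment received, report the overall and per-complication risks and the risk differences with 95% CIs. Place this beside the intention-to-treat comparison, which stays, and label it as non-randomised. State the denominator of each table.

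The cost is one sentence in the Analysis section and one extra table. No new data are needed: complications are already recorded, and treatment received is already required for the planned as-treated analyses. Recruitment is ongoing and the analysis plan is still to be finalised before database lock, so the change can be prespecified. The drawback is possible selection in the treatment-received contrast, because men who switch or never start may differ from those who follow allocation. A contrast for Clavien-Dindo grade III or higher could be added from the recorded grades, but it is optional.
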